VTE occurrence leads to suboptimal treatment of ALL patients. In 68% of CSVT patients, therapy adjustments are necessary [11], which may lead to reduced survival rates [4]. In addition, CVC-related DVT is associated with recurrent catheter complications, such as obstruction of the catheter and catheter-related infections [23].

Currently, there are no evidence-based strategies to prevent VTE complications during ALL treatment. Administration of fresh frozen plasma (FFP) or antithrombin (AT) do not reduce the risk of VTE [24]. A few prospective cohort studies have been published which use low-molecular-weight heparin (LMWH) for thromboprophylaxis during ALL treatment. Elhasid et al. reported on 41 children with ALL who received LMWH prophylaxis during 4 to 8 courses in18–24 days of L-asparaginase treatment. During 76 courses of asparaginase, none of the children developed VTE and no bleeding episodes occurred [25]. Mitchell et al. described 19 children with ALL and increased risk for thrombosis, based on a VTE-risk score, including asparaginase, steroids, presence of CVC and thrombophilia. VTE developed in 1 of 8 children who were given prophylactic dose LMWH and in 8 of 11 children without thromboprophylaxis. No bleeding events occurred [26].

However, thromboprophylaxis with LMWH during ALL treatment has not been studied in a randomized design. As the prospective cohort studies showed promising results with a negligible bleeding risk, a large randomized controlled trial is needed to confirm these findings.

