### Sample size calculation

Power calculations were based on an estimated symptomatic VTE incidence of 10% based on the previous DCOG ALL-10 study, and an estimated relative risk reduction (RRR) of 75% based on the abovementioned cohort studies with LMWH in childhood ALL [25, 26, 30, 31]. Using nQuery Advisor (7.0, 2007), it was calculated that 162 patients are required in each arm for a power of 80%, using a two-sided test with significance level α = 0.05. Hence, 324 patients will be randomized in this study.

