### Statistical analysis

All data will be analyzed according to the intention-to-treat principle. Descriptive data will be presented as mean with its corresponding standard deviation if normally distributed, and medians with ranges if data are skewed. Depending on the data distribution the Student’s *t* test or a Mann-Whitney U-test will be used to compare continuous variables between the treatment groups. Categorical variables will be analyzed using the Chi-square test.

Efficacy and safety of LMWH to prevent VTE will be analyzed by the difference between the incidence proportions and cumulative incidences of the primary efficacy and safety outcomes, symptomatic objectified VTE and major or clinically relevant non-major bleeding, respectively, observed from randomization up to 14 and 7 days after the last PEG asparaginase and Erwinia asparaginase, respectively. A two-sided test with significance level α = 0.05 will be used.

All bleeding events that occur during LMWH or within 2 days after cessation of LMWH will be included. Incidence proportions (number of children with outcome during the period divided by number of children at risk at the beginning of the period) and cumulative incidences will be estimated by a joint model to estimate event free survival for the primary safety outcome. To identify which risks factors are associated with time to VTE a joint model for longitudinal data and survival outcome will be used.

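### The Statistical analysis section assigns bleeding incidence to a joint model, which is the wrong estimator: an incidence proportion is a ratio of counts, and no longitudinal process is named for bleeding

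*Protocol article*

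**What the plan says.** All points are in the protocol article.

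- **Statistical analysis, third paragraph.** An incidence proportion is defined as the children with the outcome during a period over the children at risk when it begins. The same sentence says that these proportions and "cumulative incidences will be estimated by a joint model to estimate event free survival for the primary safety outcome".
- **Same paragraph, next sentence.** "To identify which risks factors are associated with time to VTE a joint model for longitudinal data and survival outcome will be used". Here the longitudinal component is named in general terms.
- **Statistical analysis, first paragraph.** A general rule: "Categorical variables will be analyzed using the Chi-square test". The paragraph on efficacy and safety says only that a two-sided test at 0.05 will be used on the difference in incidence proportions and cumulative incidences.
- **Aim and study design; Data and blood sample collection.** The serial measurements described are five coagulation assays, collected to study VTE. Two mutations are determined once.
- **Background.** "As the prospective cohort studies showed promising results with a negligible bleeding risk" is the only indication of how much bleeding to expect. No planning rate is given.
- **Sample size calculation.** An "estimated symptomatic VTE incidence of 10% based on the previous DCOG ALL-10 study", "an estimated relative risk reduction (RRR) of 75" percent, and the result that "162 patients are required in each arm for a power of 80" percent, "using a two-sided test with significance level α = 0.05".

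**The concern.** The joint-model sentence concerns the main safety result, and it mismatches quantity and method in two ways. First, a ratio of counts is observed directly, so sending it through a joint model adds assumptions and no information. Second, a joint model has a longitudinal submodel and a survival submodel. Bleeding has the second, but the article gives nothing for the first. Whoever programs the analysis must either invent a marker or quietly use another method. In both cases the safety analysis would be settled after the protocol, possibly with data in view.

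A further issue is how safety will be concluded. If bleeding is rare, a two-sided test has little power and a large p-value says little. What a guideline reader needs is how large an excess of bleeding the data still allow.

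**Working it through.** **1. Estimand against estimator**

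| Quantity | What it needs | What the article supplies |
|---|---|---|
| Incidence proportion of bleeding | a count and a denominator | both, in its own definition |
| Cumulative incidence of bleeding | event times, censoring, handling of competing events | event times; follow-up that ends early at ALL recurrence or death |
| Joint model for bleeding | event times and a repeatedly measured process | event times only |
| Joint model for time to VTE | event times and a repeatedly measured process | both: VTE times and serial coagulation assays |

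The third row is the defect. The coagulation assays are tied to VTE. Anti-Xa is measured after LMWH is started, so arm B, which receives none, could not contribute to it. The second row points to a competing-risk estimator, because a child who dies or relapses leaves the period of observation for bleeding.

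**2. The plan's sample size**

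Inputs: p1 = 0.10; p2 = 0.10 × (1 − 0.75) = 0.025; mean 0.0625; z = 1.960 and 0.842.

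n = [1.960 × √(2 × 0.0625 × 0.9375) + 0.842 × √(0.10 × 0.90 + 0.025 × 0.975)]² / (0.10 − 0.025)² = 162.3 per arm.

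This is 163 rounded up and agrees with the stated 162. Power at 162 is 0.799.

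**3. What zero bleeds would show**

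Exact two-sided 95% upper limit for 0/n: 1 − 0.025^(1/n).

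- n = 162: 1 − 0.025^(1/162) = 0.0225, or 2.3%.
- The two cohorts in the Background had no bleeds in 41 + 8 = 49 children on LMWH: 1 − 0.025^(1/49) = 0.073, or about 7%.

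Even the best possible result in one arm leaves a rate of 2.3% open.

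**4. Does the chi-square test mislead on bleeding?**

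The article gives no bleeding rate, so the rates are assumed. All outcomes were enumerated with 162 children per arm and equal rates in both arms.

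| Assumed rate | Size, uncorrected chi-square | Size, Fisher |
|---|---|---|
| 0.5% | 0.008 | 0.0002 |
| 1% | 0.033 | 0.003 |
| 2% | 0.045 | 0.013 |
| 3% | 0.045 | 0.020 |
| 4% | 0.048 | 0.023 |
| 5% | 0.049 | 0.026 |

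The chi-square test stays below 0.05 throughout. For an assumed true difference of 1% against 4%, power is 0.40 by chi-square and 0.26 by Fisher's exact test. Either is too low for a non-significant result to support safety.

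**5. Events for the VTE risk-factor model**

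162 × 0.10 + 162 × 0.025 = 16.2 + 4.05 = 20.25, or about 20 symptomatic VTEs over all treatment arms under the plan's own assumptions.

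**The case against.** **The article is condensed.** The full protocol or SAP may name a process for bleeding, or may use the term joint model loosely. That is possible, but the criticism does not rest on an omission. The article states an estimator for a quantity that it has just defined as a ratio, and that pairing is wrong whatever marker is added later.

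**Bleeding may not be sparse.** The Statistical analysis section counts major or clinically relevant non-major bleeding, while Aim and study design makes major bleeding alone the primary safety endpoint. The word negligible describes small cohorts and is not a planning rate. This stands: one cannot say that a bleeding model would fail for lack of events. The wrong choice of estimator does not depend on it.

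**Stronger readings that a reader might infer, and that the documents do not support:**

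- *Chi-square will give falsely significant bleeding results.* With 4 against 0 bleeds, chi-square gives p = 0.044 and Fisher p = 0.123, which looks alarming. The enumeration shows no size above 0.05 at the rates checked, so the gap reflects the conservatism of Fisher's test. The article also never ties chi-square to bleeding by name.
- *Fisher's test must replace it.* For a harm outcome that would cut power from 0.40 to 0.26 in the assumed 1% against 4% case.
- *The plan will declare safety when p exceeds 0.05.* No section states such a rule.
- *The VTE risk model is overfitted and confounded by arm.* Five assays and two mutations would give 20.25/7 = 2.9 events per candidate if all entered one model. The article does not say that they do, nor that arm is left out. For a secondary objective, a SAP would normally settle this.

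**Conclusion.** The concern holds for the bleeding estimator. The article states a joint model for a quantity that is a simple proportion and for a cumulative incidence with no longitudinal process named. This follows from the text alone and rests on no assumed rate. Its effect on the result cannot be quantified, because neither a bleeding rate nor a model specification is given. What can be quantified is precision: 0/162 still allows 2.3%, so the safety conclusion should be read from a confidence interval.

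For the VTE risk-factor model only a caution stands. The class of model suits serial assays and time to VTE, but about 20 events, assuming 10% and 2.5% incidence in 162 children per arm, support little complexity. No finding is made against the chi-square test.

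**What to change.** 1. Delete the joint model for the primary safety outcome. Report n/N per arm with exact 95% confidence intervals, and the between-arm risk difference with a score-type 95% interval (for example Miettinen-Nurminen).
2. Estimate the cumulative incidence of bleeding by the Aalen-Johansen estimator, with death and ALL relapse as competing events.
3. State that the safety conclusion rests on the confidence interval for the difference, not on a non-significant p-value. No switch to Fisher's test is needed.
4. Use one definition of the primary safety outcome across the Abstract, Aim and study design, and Statistical analysis, so that these estimates refer to a single endpoint.
5. Limit the VTE joint model to one or two pre-specified markers, include treatment arm, and label it exploratory.

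Items 1 to 3 cost a change of wording and make the programming simpler. Item 4 is a wording decision. Item 5 makes the claim for the risk model more modest. Recruitment, sample size and data collection do not change.

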### Ethical considerations

The study has been approved by the Ethics Committee of the Erasmus Medical Center in Rotterdam, the Netherlands, and the local Ethics Committee of each participating hospital. Patients can only be included in this study after obtaining written informed consent of both parents and children aged 12 and older. Verbal and written information on all parts of the study should be given.

We acknowledge, daily subcutaneous injections for the entire duration of asparaginase therapy could be a burden for patients. However, the high risk of VTE and potentially severe complications deriving from this VTE, transcend potential burden of dialy injections. Lidocain/prilocain cream will be applied to diminish the pain of subcutaneous injections. To evaluate the burden, patients will receive a booklet with questions.

### Withdrawal of patients

Children can discontinue their participation in the study at any time for any reason if they wish to do so without any consequences for their care, at their own request or at the request of their parents/legally acceptable representative. Furthermore, study medication can be stopped prematurely in case of serious adverse events, VTE requiring therapeutic anticoagulant treatment, or if, in the investigator’s opinion, study medication should be stopped for any other reason.

## Discussion

Despite the fact that thromboprophylaxis with LMWH has been proven to be safe in children for the prevention of VTE, there are no randomized studies that have investigated the use of thromboprophylaxis with LMWH during ALL treatment [32]. The TropicALL will be the first randomized controlled trial to investigate the safety and efficacy of LMWH as thromboprophylaxis in children treated for primary ALL. As a result of its incorporation in the DCOG ALL-11 and subsequent study protocols, optimal enrolment of patients is secured as well as implementation in all involved pediatric oncology centers. With the results of this study, we intend to establish (inter)national guidelines with recommendations for thromboprophylaxis during childhood ALL treatment.

## Abbreviations

ALL: Acute lymphoblastic leukemia
AT: Antithrombin
CVC: Central venous catheter
CSVT: Cerebral sinovenous thrombosis
DCOG: Dutch Childhood Oncology Group
DVT: Deep venous thrombosis
FFP: Fresh frozen plasma
GFR: Glomerular filtration rate
HIT: Heparin-induced thrombocytopenia
LMWH: Low-molecular-weight heparin
PTS: Post thrombotic syndrome
RRR: Relative risk reduction
VTE: Venous thromboembolism
